### **6.3 Scheduled Follow-ups**

Required follow-up visits will be at 1-3 months, 6-months telephone follow-up, 12-months, and 24-month telephone follow-up. Refer to **Table 2** for required follow-up testing and assessments.

### **6.4 Interim/Unscheduled Visits**

Interim/unscheduled visits will be considered those that occur in addition to the required visit interval schedule. If an unscheduled or interim visit occurs, a Follow-up eCRF should be completed to capture data collected at the visit as well as pertinent additional eCRFs (medication and adverse event assessments as applicable). In the event of a confirmed stroke or TIA, the Modified Rankin Scale eCRF should be completed 90 days after the event and echo imaging should be submitted to the core lab.

### **6.5 Sponsor Representatives**

Trained Sponsor personnel may perform certain study activities to ensure compliance to the clinical protocol and may provide technical expertise. Monitoring may be performed by SJM and/or authorized designees according to the International Organization for Standardization (ISO) 14155 and MEDDEV guidelines for post market studies; and applicable SJM standard operating procedures and work instructions. Qualified monitors will ensure investigators comply with this clinical protocol and ISO 14155 and MEDDEV post market requirements.

To ensure study personnel accept, understand and complete their assigned responsibilities, monitors, field clinical personnel, and/or clinical country managers, may perform periodic site visits during the course of the study. These actions will help to ensure the continued acceptability of the facilities, compliance to the clinical protocol and relevant regulations, and the maintenance of complete records.

Monitoring will include review and resolution of missing or inconsistent results and source document verification (i.e. comparison of submitted study results to original reports) to assure the accuracy of the reported data.

Sponsor representatives will periodically request source documents, resolution of discrepancies, submission of echocardiography imaging etc. for data cleaning and reporting purposes.

## **6.6 Subject Study Completion**

After the 2-year follow-up visit is completed, subjects will be discontinued from the study and return to receiving medical care per their physician's recommendations.

## **6.7 Compromising Factors**

This is an observational post-market study evaluating real-world outcomes in subjects with LAAO. There are no anticipated or foreseeable factors that may compromise the outcome of the study or interpretation of results.

## **6.8 Subject Withdrawal**

Subjects must be informed about their right to withdraw from the study at any time and for any reason without sanction, penalty, or loss of benefits to which the subject is otherwise entitled. Withdrawal from the study will not jeopardize their future medical care or relationship with the investigator. Subjects will be asked to specify the reason for their termination, but have the right not to answer.

The investigator may decide to withdraw a subject from the study at any time with reasonable rationale. The subject's future care will not be influenced by a decision, voluntary or otherwise, to withdraw from the study. All reasonable efforts should be made to retain the subject in the study until completion of the study.

Reasons for subject withdrawal include, but are not limited to:

- Subject withdraws consent
- Subject refuses to continue their participation
- Subject does not meet the inclusion/exclusion criteria (withdraw attempt to treat subjects 7 days after the date of the attempted procedure)
- Subject is deceased (event or symptoms pertaining to outcome of death must be documented on an Adverse Event eCRF)
- Subject's participation is terminated by the PI or investigator, although the subject consented, since participation is no longer medically appropriate
- Subject is 'lost to follow up' (subject does not adhere to the scheduled follow up visits but has not explicitly requested to be withdrawn from the study)
- Site personnel should make reasonable efforts to locate and communicate with the subject in order to achieve subject compliance to the scheduled follow up visits

If a subject withdraws from the study, the site will record the subject's reasons for withdrawal on the Withdrawal eCRF.

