## **4.3 Objectives**

### **4.3.1 Primary objectives**

The Amulet observational post-market study has four primary objectives:

1. Assessment of acute (0 - 7 days post procedure) serious adverse events
2. Assessment of late (> 7 days post-procedure) serious adverse events through 2 years
3. Report the percentage of stroke (ischemic), systemic embolism, and cardiovascular death through 2 years
  - Cardiovascular death is defined as (see **Appendix L**) death due to proximate cardiac cause, death caused by non-coronary, non CNS vascular conditions, death from vascular CNS causes, hemorrhagic stroke, ischemic stroke, all procedure related deaths, sudden or unwitnessed death and death of an unknown cause

4. Report the percentage of bleeding events through 2 years

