| L abile INR (Unstable/high INR's, or poor time (< 60% time in therapeutic range)                    | 1            |
| E lderly - Age ≥ 65 years                                                                           | 1            |
| D rugs - Medication usage predisposing to bleeding (antiplatelet agents, NSAIDs)                    | 1            |
| A lcohol usage history (> 8 drinks/week)                                                            | 1            |

The principal investigator or delegated study personnel is responsible for screening potential subjects to determine subject eligibility for the study. Enrollment information (date of consent, inclusion/exclusion information, etc.) will be recorded in the subject's hospital records and on the Baseline and Inclusion/Exclusion eCRF. The Inclusion/Exclusion eCRF should be submitted within one week and will serve as notification of enrollment to the Sponsor upon receipt.

If a subject does not meet all inclusion criteria or meets any of the exclusion criteria, the subject cannot participate in the study. The Baseline/Screening and Inclusion/Exclusion eCRFs should be completed, in addition to the Withdrawal eCRF (consented screen failure), as applicable. If the subject was enrolled (i.e. consented and the dilator/delivery system introduced), but meets the exclusion criteria during the procedure, the Baseline, Inclusion /Exclusion, Procedure, and Withdrawal eCRFs (complete 7 days after the attempted procedure) should be completed.

Serious adverse events will be reported from the time the dilator/device delivery system has been introduced to the time the subject concludes the study. An Adverse Event eCRF should be completed, as applicable.

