#### **8.1.2 Assessing, recording and reporting serious adverse events, serious adverse device effects, and device deficiencies/complaints**

Safety surveillance within this study and the safety reporting performed both by the investigator and Sponsor starts as soon as the dilator/device delivery system has been introduced. The safety surveillance and the safety reporting will continue until the last visit has been performed, the subject is deceased, the subject/investigator concludes their participation into the study or the subject/investigator withdraws the subject from the study.

All serious adverse events (including deaths), serious adverse device effects, and device deficiency information (if applicable) will be collected throughout the clinical study and reported to the Sponsor. Investigators will record all serious adverse events, serious adverse device effects, and deaths on the appropriate eCRF. Device deficiencies will be reported per country reporting timeline requirements to the Sponsor outside of the database on an Event Report Form (**Appendix I**).

For any serious adverse event (including deaths) and any serious adverse device effect, the investigator shall notify the Sponsor immediately of the investigator's awareness of the event and provide the Sponsor with all necessary documentation needed. Device deficiencies will be reported to the Sponsor outside of the database on an Event Report Form (**Appendix I**), as soon as possible after first learning of the event.

Records relating to the subject's subsequent medical course must be maintained and submitted (as applicable) to the Sponsor until the event has subsided or, in case of permanent impairment, until the event stabilizes and the overall clinical outcome has been ascertained. Additional

information may be requested, when required, by the Sponsor in order to support the reporting of serious adverse events to the CEC, regulatory authorities and/or other authorities.

Serious adverse events and serious adverse device effects should be monitored by the investigator until resolved. The status of the subject's condition should be documented at each follow-up visit.

Events reportable to the Sponsor, EC, CAs and regulatory authorities (as applicable) include:

- All serious adverse device effects
- All serious adverse events (including deaths and whether or not the event is considered device or procedure related)

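### Investigator withdrawal ends outcome collection in implanted subjects, so the 2-year percentages are understated if such withdrawals follow clinical deterioration

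*Protocol*

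**What the plan says.** Section 6.8 of the protocol gives the investigator a general power: "The investigator may decide to withdraw a subject from the study at any time with reasonable rationale". Its list of withdrawal reasons, which is expressly not exhaustive, includes "Subject's participation is terminated by the PI or investigator, although the subject consented, since participation is no longer medically appropriate". The protocol does not define when participation stops being medically appropriate. The same section also asks for retention: "All reasonable efforts should be made to retain the subject in the study until completion of the study".

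Two places fix what happens to data collection. Section 8.1.2 ends safety surveillance and reporting at the last visit, at death, or when "the subject/investigator concludes their participation into the study or the subject/investigator withdraws the subject from the study". Section 6.1 gives the same window: "Serious adverse events will be reported from the time the dilator/device delivery system has been introduced to the time the subject concludes the study". Section 8.1.2 adds, for events already known, "Serious adverse events and serious adverse device effects should be monitored by the investigator until resolved".

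The outcomes affected are 2-year quantities. Section 4.3.1 sets as objective 3 "Report the percentage of stroke (ischemic), systemic embolism, and cardiovascular death through 2 years" and as objective 4 "Report the percentage of bleeding events through 2 years"; objective 2 is late serious adverse events through 2 years. Section 12 counts in the numerator the subjects with the event. The denominator is those subjects plus the event-free subjects who reach 2 years.

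**The concern.** The device is a permanent implant and no study treatment is being given that could be stopped. After the 1-3 month visit with its transoesophageal echocardiogram (TOE), Table 2 schedules only a 6-month phone contact, a 12-month visit and a 24-month phone contact, all for medication and adverse events. A further TOE and a 90-day Rankin assessment follow only a confirmed stroke or transient ischemic attack. A test may become medically unsuitable for a subject; asking whether an event has occurred rarely does. Yet nothing in the protocol separates stopping a test or visit from stopping the collection of outcomes, and nothing provides for vital status or events after withdrawal.

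One listed ground for withdrawal is medical. If it is used for subjects whose condition is worsening, those who leave have a higher risk of a later event than those who stay. The reported percentage then describes subjects who were kept in the study rather than all subjects over 2 years from implant. The loss acts endpoint by endpoint. A subject withdrawn after a serious bleed is counted for objective 4 but disappears from objective 3 if no objective 3 event has yet occurred. A statistical analysis plan, which was not available here, could choose another estimator, but it could not recover events that the protocol stops collecting.

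**Working it through.** There is no figure in the protocol to reproduce. The sample of about 1000 subjects (Section 4.2.2) has no stated event rate, dropout rate or precision target behind it, and Section 12 tests no hypothesis.

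**Step 1: how a withdrawn subject is handled.** An implanted subject is withdrawn by the investigator before 2 years without the event in question. Reporting ends (Sections 8.1.2 and 6.1). The subject has no recorded event and has not reached 2 years, so under Section 12 the subject is in neither numerator nor denominator. A later event is unrecorded.

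**Step 2: formula.** Let w be the share withdrawn while still event-free, rw their risk from withdrawal to 2 years, and r0 the 2-year risk in the rest.

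- Reported rate = r0
- Full rate = w × rw + (1 − w) × r0
- Relative understatement = 1 − reported / full

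**Step 3: inputs.** All three are assumptions: w = 1%, 3%, 5%; rw = 30%, 50%; r0 = 6%, 10%. N = 1000 is from the protocol, and the exact 95% interval is the method named in Section 12.

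**Step 4: results.** The interval is the one that would be reported on the (1 − w) × 1000 subjects who remain, with the event count rounded to a whole number.

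| r0 (reported) | w | rw | Full rate | Gap (points) | Relative understatement | Reported 95% CI |
|---|---|---|---|---|---|---|
| 6% | 1% | 30% | 6.24% | 0.24 | 3.8% | 4.6-7.6% |
| 6% | 1% | 50% | 6.44% | 0.44 | 6.8% | 4.6-7.6% |
| 6% | 3% | 30% | 6.72% | 0.72 | 10.7% | 4.6-7.7% |
| 6% | 3% | 50% | 7.32% | 1.32 | 18.0% | 4.6-7.7% |
| 6% | 5% | 30% | 7.20% | 1.20 | 16.7% | 4.6-7.7% |
| 6% | 5% | 50% | 8.20% | 2.20 | 26.8% | 4.6-7.7% |
| 10% | 1% | 30% | 10.2% | 0.20 | 2.0% | 8.2-12.0% |
| 10% | 1% | 50% | 10.4% | 0.40 | 3.8% | 8.2-12.0% |
| 10% | 3% | 30% | 10.6% | 0.60 | 5.7% | 8.2-12.1% |
| 10% | 3% | 50% | 11.2% | 1.20 | 10.7% | 8.2-12.1% |
| 10% | 5% | 30% | 11.0% | 1.00 | 9.1% | 8.2-12.1% |
| 10% | 5% | 50% | 12.0% | 2.00 | 16.7% | 8.2-12.1% |

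One row written out, for w = 3%, rw = 50%, r0 = 10%: 0.03 × 0.50 + 0.97 × 0.10 = 0.015 + 0.097 = 0.112, and 1 − 0.100 / 0.112 = 10.7%. In that case 0.03 × 1000 × 0.50 = 15 events are missed. The full rate lies outside the reported interval in one row of twelve (6%, 5%, 50%).

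**Step 5: the same rule when withdrawal is unrelated to risk.** If rw = r0, the formula gives no understatement. If 5% of subjects are withdrawn independently of risk, and half of a 10% risk has accrued by then, events before withdrawal still count: 950 × 0.10 + 50 × 0.05 = 97.5 events over 950 + 2.5 = 952.5 subjects, or 10.2%. This slightly overstates 10%. The direction of the bias therefore depends on the link between withdrawal and risk.

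**The case against.** The strongest reply is that the medical ground is one entry in a list that reads largely as a set of reasons for the Withdrawal form, and that also includes death and loss to follow-up. It names neither implanted subjects nor deterioration. Because the list also covers attempted procedures without an implant, the entry fits equally well a consented subject found unfit before or during the procedure. Section 6.8 itself asks sites to retain subjects. This stands as a limit. A reader might infer that the protocol directs sites to drop implanted subjects who get worse, or to do so against their wish to continue. The text supports neither: the clause is permissive, and its reference to consent may mean only consent at entry.

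The second reply is that much of the deterioration is already counted. Illness that is life-threatening, leads to hospital admission or leaves permanent impairment is itself a serious adverse event under Section 8.1, so a late one counts for objective 2. A disabling bleed counts for objective 4. Open events are followed to resolution. This also stands, and it narrows the loss to a new objective 3 event, a first bleed or a first late serious adverse event after withdrawal. Neither the retention sentence nor the follow-up of open events captures those.

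The third reply concerns size. If little in late follow-up can become medically inappropriate, such withdrawals may be rare, and at about 1% the effect is small. No threshold is tested that a shift could cross. Both points are fair. They limit the weight of the concern but do not remove the mechanism.

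**Conclusion.** The point holds in conditional form. By the protocol's own rules, an investigator withdrawal for any reason stops event collection in an implanted subject and removes the subject from the 2-year rate if still event-free. If such withdrawals are linked to clinical deterioration, objectives 3 and 4 and first late serious adverse events are understated. Under the assumed inputs the relative understatement runs from 2% to 27%, and is about 0.2-0.4 percentage points at 1% withdrawn. None of those inputs comes from the protocol.

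A reader might conclude that the bias necessarily flatters the device. The documents do not establish that: they give no frequency or reasons for such withdrawals, and without a link to risk there is no understatement. The statement in Section 6.7 that no foreseeable factor could compromise interpretation is nonetheless too strong while this route is open. The change is worth making because it is cheap and the lost events may not be recoverable afterwards.

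**What to change.** Deleting the one listed reason would not be enough, since the general discretion and the open-ended list would remain. Instead:

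- In Section 6.8, state that for implanted subjects investigator withdrawal, for whatever reason, ends only the study tests or visits judged inappropriate. Vital status, stroke, systemic embolism, bleeding and serious adverse events continue to be collected at the 6-, 12- and 24-month contacts, by phone, proxy or medical record, unless the subject withdraws consent to this.
- In Sections 8.1.2 and 6.1, amend the end of the reporting window so that investigator withdrawal does not end surveillance of an implanted subject.
- Report the number of investigator withdrawals by reason, so that a reader can judge how far the rates could be affected.

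The cost is a few sentences of protocol text and contacts that are already in the schedule. It changes data collection only, not clinical care. The small downside is that some data will come from proxies or records rather than from the subject.

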## **7. COMPLIANCE STATEMENTS**

The study will be performed in accordance with the most current versions of the World Medical Association (WMA) Declaration of Helsinki (**Appendix C**), ISO 14155, MEDDEV post market requirements and any regional and/or national regulations and will be compliant to these International Standards and any regional and national regulations, as appropriate.

The investigator will not enroll subjects or obtain informed consent from any subject prior to obtaining EC approval, if applicable, and authorization from the Sponsor in writing for the study. The subject must sign the study informed consent form prior to any study-related procedures.

If additional requirements are imposed by the EC, those requirements will be followed, if appropriate. If any action is taken by an EC, and regulatory requirements with respect to the study, that information will be forwarded to SJM.

As the Sponsor, SJM has taken general liability insurance in accordance with the requirements of applicable local laws. Appropriate SJM country representatives will be utilized to interpret the requirements regarding the type of insurance that will be provided to subjects, and such information will be incorporated into the informed consent form, as applicable. If required, additional subject coverage or study specific insurance may also be provided by the Sponsor.

## **8. SERIOUS ADVERSE EVENTS, SERIOUS ADVERSE DEVICE EFFECTS, DEATHS AND DEVICE DEFICIENCIES**

Risks associated with the Amulet device are similar to other implantable cardiac occlusion devices. Some of the potential risks include but are not limited to those listed below. The definitions noted below are used for the purposes of this study. Radiation risks associated with the procedure are comparable to a diagnostic catheterization procedure.

Only serious adverse events (SAEs) will be collected for this study. Serious adverse events are classified as serious adverse events or serious adverse device effects (SADEs). A planned hospitalization for a pre-existing condition is not considered a serious adverse event.

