### **8.1 Serious Adverse Events**

A serious adverse event is an adverse event that led to:

- Death
- A serious deterioration in the health of the subject, that either resulted in:
  - A life-threatening illness or injury OR
  - A permanent impairment to a body structure or a body function OR
  - An in-patient or prolonged hospitalization OR
  - A medical or surgical intervention to prevent life-threatening illness or injury or permanent impairment to a body structure or a body OR
  - A malignant tumor OR
  - Fetal distress, fetal death or a congenital abnormality or birth defect

Potential serious adverse events include but are not limited to:

- **Air Embolus** – symptomatic event resulting from the introduction of air into the circulatory system
- **Allergic reaction** – idiosyncratic reaction to the device implanted or to nickel
- **Anesthesia reaction** – undesired reaction to anesthetic agent
- **Arrhythmia** – cardiac rhythm disturbance
- **Bleeding** – *\*see definition of bleeding as defined by BARC at end of section*

- **Cardiac arrest** – failure of the heart to contract
- **Cardiac tamponade** – constriction of the heart causing inefficient contraction resulting from accumulation of excess fluid in the pericardium
- **Death** – permanent cessation of all vital bodily functions
- **Device embolization** – movement of the device from its intended location
- **Device migration** – movement of the device within its intended location
- **Embolic event** – acute vascular insufficiency or occlusion of the extremities or any non-central nervous system organ associated with clinical, imaging, surgical/autopsy evidence of arterial occlusion in the absence of other likely mechanism (e.g., trauma, atherosclerosis, or instrumentation). When there is presence of prior peripheral artery disease, angiographic or surgical or autopsy evidence is required to show abrupt arterial occlusion
- **Fever** – defined as a body temperature  $> 37.5$  or  $38.3$  °C ( $99.5$  or  $100.9$  °F)L
- **Foreign body embolization** – movement of device material, delivery system material, or other material from its intended location
- **Hypotension** – sustained systolic blood pressure  $< 90$  mmHg
- **Hypertension** – systolic blood pressure of  $> 160$  mmHg
- **Infection** – invasion and growth of a pathogenic organism within the body

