**\*Bleeding**

Classified as Type 0 – 5 according to the following BARC definitions:

**Type 0**: No bleeding

**Type 1**: Bleeding that is not actionable and does not cause the patient to seek unscheduled performance of studies, hospitalization, or treatment by a healthcare professional; may include episodes leading to self-discontinuation of medical therapy by the patient without consulting a healthcare professional

**Type 2 (minor)**: Any overt, actionable sign of hemorrhage (e.g. more bleeding than would be expected for a clinical circumstance, including bleeding found by imaging alone) that does not fit the criteria for Type 3, 4, or 5 but does meet at least one of the following criteria: (1) requiring nonsurgical, medical intervention by a healthcare professional, (2) leading to hospitalization or increased level of care, or (3) prompting evaluation

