#### Thrombus

If a thrombus is detected post- procedure, complete an Adverse Event eCRF. The following data will be collected on the CRFs:

- Medication regime at time thrombus
- Medication(s) used to treat thrombus
- Imaging performed to monitor thrombus and frequency of monitoring
- Timeframe for resolution

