## **12. STATISTICAL METHODS**

No formal hypothesis will be tested for this observational post-market study. However, point estimates and exact 95% confidence intervals will be provided for the following rates in the study:

- Procedural serious adverse events (0 - 7 days) post procedure or before hospital discharge whichever latest) will be summarized for all subjects as well as stratified by imaging modality used for implanting the device (TOE and ICE)
- Late serious adverse events through 2 years
- Occurrence of ischemic stroke , systemic embolism and cardiovascular death through 2 years
- Occurrence of bleeding (including hemorrhagic stroke) events through 2 years

Data collected on the following objectives will also be reported:

- Technical success (secondary objective)
- Procedural success (secondary objective) - This objective will be summarized for all subjects as well as stratified by imaging modality used for placement of the device (TOE and ICE)
- OAC usage through 2 years (secondary objective)

- Serious Adverse Events – this may include, but is not limited to:
  - Significant bleeding events (e.g. cardiac tamponade, central nervous system (CNS) bleeding, and any bleeding related to the device or procedure that necessitates an operation)
  - Endocarditis
  - Device embolization (summarized by those that can be snared, and those that require surgical intervention)
  - Thrombus on device
  - All strokes
  - Transient ischemic attacks
  - Systemic embolism
  - Cardiovascular death
- Closure at procedure and 1-3 months post implant
  - The echo core lab's adjudication of residual flow will be used for this analysis. The following guidelines will be used:
    - None – No color flow jet in or out of the LAA
    - Small leak: < 3 mm diameter jet by color flow Doppler
    - Medium leak: 3-5 mm diameter by color flow Doppler
    - Large leak: > 5 mm diameter jet by color flow Doppler

Other variables may be summarized as deemed appropriate. The numerator for all rates will be the number of subjects who experience the corresponding event. The denominator for all rates will be subjects who experience the corresponding event plus all other subjects who achieve 2-years of follow-up.

Version 9.0 or higher of the SAS® statistical software package or other widely accepted statistical software will be used to provide all statistical analyses. Unless otherwise stated, attempts will not be made to adjust for multiple comparisons.

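### Primary objective 4 is labelled as all bleeding through 2 years, but the protocol collects only serious adverse events, so the figure it yields is a serious-bleeding rate

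*Protocol*

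**What the plan says.** Protocol Section 4.3.1, objective 4: "Report the percentage of bleeding events through 2 years". Section 12 promises a point estimate and exact 95% confidence interval for the matching quantity: "Occurrence of bleeding (including hemorrhagic stroke) events through 2 years". Neither sentence limits severity.

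Section 8 opens its list of events with "The definitions noted below are used for the purposes of this study". In Section 8.1 the entry for bleeding points the reader onward: "see definition of bleeding as defined by BARC at end of section". The definition that follows reproduces BARC Types 0 to 5, with Type 1 described as "Bleeding that is not actionable and does not cause the patient to seek unscheduled performance of studies, hospitalization, or treatment by a healthcare professional".

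The collection rule, also in Section 8, is "Only serious adverse events (SAEs) will be collected for this study". Section 6.1 repeats that the reporting duty covers serious events, from introduction of the delivery system until the subject leaves the study. Section 13.2 has the clinical events committee adjudicate serious adverse events.

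**The concern.** Bleeding is one of four primary results. Its wording and its definition cover every grade of bleeding, while the collection rule admits only part of that range. If the plan is followed exactly, the report will carry a percentage headed bleeding events that counts serious bleeds only. A reader who takes the heading at face value, or sets it beside a rate that counts lesser bleeds, would be misled. The gap arises at data collection, so no analysis plan can recover events that were never recorded.

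**Working it through.** The protocol states no bleeding rate, BARC mix, power or sample-size derivation, so there is no figure to reproduce. The check sets the BARC types against the seriousness criteria, then shows how the Section 12 formula behaves.

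**Step 1. BARC types against the Section 8.1 criteria.** An event is serious if it led to death, life-threatening illness or injury, permanent impairment, admission or prolonged stay, an intervention to prevent life-threatening illness or permanent impairment, malignancy, or fetal harm.

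| BARC type | What the definition requires | Captured under the SAE-only rule? |
|---|---|---|
| 1 | Not actionable; no unscheduled studies, admission or treatment sought | Never |
| 2 | Any one of: non-surgical treatment; admission or higher level of care; evaluation | If admitted, yes. If only evaluated or treated as an outpatient, only when another criterion is met |
| 3a | Transfusion, or hemoglobin fall of 3 to under 5 g/dL | Not by definition; depends on admission or the purpose of treatment |
| 3b to 5 | For example tamponade, surgery, intracranial bleeding, death | Would ordinarily meet a criterion |

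**Step 2. Is there another route in?** Table 2 lists an adverse event assessment at each follow-up visit and Section 6 lists an Adverse Event eCRF, but no passage opens either to non-serious bleeding. The might-have-led clause in Section 8.1.1 is itself framed around serious events related to the device or procedure.

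**Step 3. Does the text elsewhere mean serious?** Objectives 1 and 2 use the word serious; objective 4 does not. Section 12 lists a narrower category separately under serious adverse events: "Significant bleeding events (e.g. cardiac tamponade, central nervous system (CNS) bleeding, and any bleeding related to the device or procedure that necessitates an operation". The note to BARC Type 4 excludes certain bypass-related bleeds from counting as bleeding events. There is no such exclusion for other Type 1 or 2 bleeds.

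**Step 4. Effect on the estimate.** Section 12 counts subjects with the event, E, over E plus all other subjects who reach 2 years. N = 1000 comes from Section 4.2.2. Three inputs are assumptions:
- p, the true 2-year percentage with any BARC 1 to 5 bleed
- s, the share of those bleeders with at least one serious bleed
- d, the non-completion among subjects without a counted event

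Then E = N·p·s and reported rate = E / [E + (1 − d)(N − E)]. For p = 10%, s = 75%, d = 20%: E = 75, denominator = 75 + 0.8 × 925 = 815, rate = 9.2%.

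Reported percentage with exact 95% interval, p = 10%:

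| d | s = 100% | s = 90% | s = 75% | s = 50% |
|---|---|---|---|---|
| 0% | 10.0 (8.2–12.0) | 9.0 (7.3–10.9) | 7.5 (5.9–9.3) | 5.0 (3.7–6.5) |
| 10% | 11.0 (9.0–13.2) | 9.9 (8.0–12.0) | 8.3 (6.6–10.2) | 5.5 (4.1–7.2) |
| 20% | 12.2 (10.0–14.6) | 11.0 (8.9–13.4) | 9.2 (7.3–11.4) | 6.2 (4.6–8.1) |

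With p = 20% and d = 0 the row reads 20.0, 18.0, 15.0 and 10.0.

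Within each row, any s below 100% lowers the figure. Down each column, non-completion raises it, because event-free non-completers leave the denominator. The two biases cancel when s = (1 − d)/(1 − p·d). For p = 10% this is 0.9/0.99 = 0.91 at d = 10% and 0.8/0.98 = 0.82 at d = 20%.

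**The case against.** The best reply is that serious bleeding was meant all along. Objective 4 does not mention BARC. The scale appears only as the definition of an entry in a list of potential serious adverse events, under a section that openly collects nothing else. The presence of Type 0, which is no bleeding, suggests that a published scale was copied whole. On that reading serious bleeds are collected and then graded, and nothing is undercounted. This is arguable, but it turns the defect into a wrong label rather than removing it, and the contrast with objectives 1 and 2 and with the separate list in Section 12 tells against it.

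It is also fair that the study tests no hypothesis and has no comparator, that Section 8.1 gives all sites written criteria, and that an independent committee adjudicates what is reported. These points limit the consequences. The committee cannot adjudicate what never reaches it. The case report forms are held under separate cover, so their bleeding fields cannot be seen.

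A reader might extend the point to device thrombus, which Section 12 reports under serious adverse events. The documents do not support the same criticism. Section 8.1 instructs: "If a thrombus is detected post- procedure, complete an Adverse Event eCRF". That specific instruction already works as an exception to the general rule. At most, the rule could cross-refer to it.

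**Conclusion.** The mismatch stands. As written, primary objective 4 would deliver a serious-bleeding percentage under the label of all bleeding: Type 1 is excluded by definition, and Types 2 and 3a are excluded whenever no seriousness criterion is met. Relative to the all-BARC rate under the same formula, the reported rate is lower whenever at least one subject has only non-serious bleeds.

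Three stronger statements are tempting and are not supported:
- **A specific percentage shortfall.** The protocol holds no bleeding rate or BARC mix, and any figure simply restates the assumed serious share. The table above is an illustration.
- **The published figure must lie below the true risk.** The completer denominator pushes upward. With a true 10% and 20% non-completion, the net result is too low only if the serious share is below about 0.82.
- **The endpoint has to become BARC 3 to 5.** That is one coherent choice among several. What the protocol needs is agreement between the endpoint and the collection rule.

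**What to change.** Make the endpoint and the collection rule agree, in one of two ways.

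(a) Restate objective 4, in the synopsis and Section 4.3.1, and the Section 12 bullet as serious bleeding events, including hemorrhagic stroke, tabulated by BARC type. The cost is wording and a narrower stated endpoint. The data are unchanged.

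(b) Name the BARC types that count, for example 3 to 5 or 2 to 5. Then require every such bleed on the Adverse Event eCRF and sent to the clinical events committee whether or not it meets a seriousness criterion, and write that exception into Sections 6.1, 8 and 13.2. The cost is a few non-serious forms and adjudications; the visit assessments already exist. This option helps only from the time it takes effect, so it should be settled before events accrue.

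Under either option, add to the SAE-only sentence in Section 8 a cross-reference to the thrombus instruction in Section 8.1 as an exception.
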